### Phase 3: Evaluation of gamified in uncontrolled environment

Phase 3 comprises a noninferiority, investigator-blinded, randomized clinical trial with two distinct groups: the intervention and control groups. Participants within the intervention group (IG) will install the gamified application on their smartphones and use a biosensor during exercise sessions. These sessions will align with the prescribed intensity derived from the ISWT, following the 6-week regimen detailed in phase 2. Participants will be duly instructed to cease exercising if they experience symptoms like chest pain, discomfort, or dizziness.

Within the gamified application, participants will have access to a diary feature, enabling them to log notifications received and their efforts during exercise, both monitored by the biosensor and the gamified app. On the other hand, individuals in the control group (CG) will receive instructions to engage in physical activity at home without biosensor monitoring. They will use the app independently, aiming for a minimum of 300 min per week at moderate intensity or at least 150 min per week at vigorous intensity (self-assessed).

Preceding and following the 6-week period, both the IG and CG will undergo assessments akin to those conducted in phase 1. These include evaluations of functional capacity, muscle oxygenation, and further assessments led by trained and blinded researchers.

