### Strategies to improve adherence to interventions {11c}

Following participant randomization, the research team will refrain from implementing specific operational measures to ensure the desired follow-up level. This approach aligns with one of the study’s primary objectives, which is to assess exercise adherence facilitated by gamification. What will be done is to send a standard message weekly to both groups requesting weekly recording of the activity carried out during the week in a spreadsheet.

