### Outcomes {12}

Primary outcomes will encompass the following: (1) the concordance between HR and step count measurements assessed by the biosensor under test compared to standard devices (Polar H10 and ActiGraph, respectively); (2) participant perception regarding the utility of the gamified application for exercise engagement; (3) comparison with the prevalence of adherence to the physical activity protocol between the control and intervention groups; (4) evaluation of exercise capacity through ISWT, including stage and the corresponding phase at which the test was halted; and (5) measurement of oxygen consumption (VO_2_).

Secondary outcomes will include the following: (1) tissue oxygenation assessed via near-infrared spectroscopy (NIRS), (2) subjective perception of exertion during ISWT, (3) evaluation of endothelial function, and (4) assessment of autonomic function.

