### Plans to promote participant retention and complete follow-up {18b}

Since one of the study’s goals is to assess the impact of gamification on adherence to PA, no specific measures will be undertaken during the study to bolster adherence. Upon the study’s conclusion, all participants will be contacted for a final assessment. For measuring adherence, the intervention group will register their adherence via a dedicated application. Meanwhile, the control group will be guided to record their physical activities on a weekly basis added to plans to promote participant retention and complete follow-up.

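### Adherence, the outcome on which Phase 3 is sized, is assigned a different recording source in each arm, and no section names one common source for the comparison

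*Protocol article*

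**What the plan says.** Outcomes {12} lists as primary outcome (3) the "comparison with the prevalence of adherence to the physical activity protocol between the control and intervention groups". Sample size {14} rests on that outcome alone: 70% against 50% adherent, 104 per arm, 149 per arm after allowing for 30% losses. Statistical methods {20a} counts a participant as adherent at 70% or more of what was prescribed.

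Three sections bear on how adherence is recorded:

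- **Section {18b}** assigns the source by arm, the intervention group (IG) first and the control group (CG) second: "the intervention group will register their adherence via a dedicated application. Meanwhile, the control group will be guided to record their physical activities", the latter weekly.
- **Phase 3 description.** IG participants log their effort in an in-app diary, "both monitored by the biosensor and the gamified app". CG participants are told to "engage in physical activity at home without biosensor monitoring. They will use the app independently", with a weekly target whose intensity they judge themselves: "at least 150 min per week at vigorous intensity (self-assessed").
- **Section {11c}.** The team will "send a standard message weekly to both groups requesting weekly recording of the activity carried out during the week in a spreadsheet".

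Section {17a} states that participants cannot be blinded.

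**The concern.** The between-arm difference in adherence is interpretable as an intervention effect only if adherence is recorded in the same way in both arms. Section {18b} is the one place that says how adherence is measured, and it splits the source by arm. Both records then pass through a single 70% cut-off, so a modest difference in recording can move participants across the line in one arm only.

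The usual safeguards do not reach this problem. The blinded researcher of sections {16c} and {17a} carries out the functional assessments, whereas the participants themselves make the adherence record and know their arm. Randomisation and the intention-to-treat analysis of section {20c} do not remove an error that arises from the arm's own instrument. A larger sample does not remove it either.

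**Working it through.** **Inputs from the protocol article.** Adherence 70% (IG) and 50% (CG), 95% confidence, 80% power, 1:1 allocation, 104 per arm, 30% losses, 149 per arm (all section {14}).

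**Assumptions.** Two-sided α = 0.05 and a pooled two-proportion test, with and without continuity correction. The documents give no error rates for either instrument, so every rate below is assumed.

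**1. The plan's own figure.** With p̄ = 0.60:

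n = [1.96·√(2·0.6·0.4) + 0.8416·√(0.21 + 0.25)]² / 0.20² = 93 per arm.

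With continuity correction: (93/4)·[1 + √(1 + 4/(93·0.20))]² = 102.8, so 103, against 104 stated. Losses: 104/0.70 = 148.6, so 149. The sample size arithmetic is not at issue.

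**2. Recorded adherence under imperfect capture.** Recorded p = Se·p + (1 − Sp)·(1 − p), where Se is the share of adherent participants recorded as adherent and 1 − Sp is the share of non-adherent participants recorded as adherent.

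- CG over-records (Se = 1, true 50%): Sp = 0.9 gives 0.50 + 0.10·0.50 = 55%; Sp = 0.8 gives 60%.
- CG under-records (Sp = 1, true 50%): Se = 0.8 gives 40%.
- IG app misses adherent participants (Sp = 1, true 70%): Se = 0.95 gives 66.5%; Se = 0.90 gives 63%.

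**3. Chance of a significant result.** Φ{(|d| − c − 1.96·s0)/s1}, where d is the recorded difference, s0 = √(2p̄(1 − p̄)/n), s1 = √[(p1(1 − p1) + p2(1 − p2))/n], and c = 0 or 1/n (continuity correction). Example, 70% v 55% at n = 104: s0 = 0.0671, s1 = 0.0663, (0.15 − 1.96·0.0671)/0.0663 ≈ 0.28, Φ = 0.61.

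| Scenario, n = 104 per arm | Recorded IG v CG | Uncorrected | Corrected |
|---|---|---|---|
| Design, no error | 70% v 50% | 84.3% | 80.5% |
| CG over-records, Sp 0.9 | 70% v 55% | 60.9% | 55.3% |
| CG over-records, Sp 0.8 | 70% v 60% | 32.6% | 27.5% |
| IG capture, Se 0.95 | 66.5% v 50% | 67.7% | 62.4% |
| IG capture, Se 0.90 | 63% v 50% | 47.2% | 41.7% |
| No true effect, CG over-records, Sp 0.8 (IG appears worse) | 50% v 60% | 30.4% | 25.7% |
| No true effect, CG under-records, Se 0.8 (IG appears better) | 50% v 40% | 30.4% | 25.7% |

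The last two rows compare with a nominal 2.5% in that direction.

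**4. If all 149 per arm contribute.** Power is 73–77% at 70% v 55% and 39–44% at 70% v 60%. The false result at a 10-point instrument difference rises to 37–41%. More participants recover some power but make a spurious difference easier to declare.

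**5. The sections side by side.** Section {18b} gives app against own record; section {11c} gives a spreadsheet in both arms; the Phase 3 description gives the app in both arms but the biosensor in IG only. The CG record of {18b} may be the {11c} spreadsheet, but the article does not say so, and {18b} does not use the spreadsheet for IG.

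**The case against.** Much can be said against a harder version of this point, and most of it stands.

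- **Sensor against self-report.** A reader might infer that IG adherence means sensor-confirmed minutes at target heart rate. The article does not say so. Section {18b} mentions only the app, where registering may include manual entry. The biosensor appears in the Phase 3 description, and the 70% rule does not require confirmed intensity.
- **The control arm also uses the app.** The Phase 3 description says so, although section {14} says controls receive guidelines only. This is a conflict to reconcile. It does not make the source common.
- **The spreadsheet is not discarded.** Section {11c} still requests it from both arms. It is simply never named as the source for the comparison.
- **No result could be attributed to gamification.** That inference goes too far. If the only error were over-recording by controls, a significant IG advantage would be conservative. A false IG advantage needs CG under-recording or inflated IG registration, which the documents neither show nor exclude.
- **App failures.** Section {20a} plans to count them and says that serious errors must be dealt with before Phase 3. That mitigates the risk of missed sessions in IG but leaves two instruments.
- **The biosensor is part of the intervention,** so some asymmetry is unavoidable. That is true of the sensor data, but not of the choice of primary adherence source.
- **A common spreadsheet would still be unblinded self-report,** and IG would complete it with device feedback that CG lacks. This is correct and limits what the fix achieves.

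**Conclusion.** The point holds as a defect in how the outcome is defined. The only section that says how adherence is measured gives each arm its own source, two other sections point elsewhere, and none names a common source for the comparison that Phase 3 is sized on. The adherence difference can therefore mix the intervention effect with an instrument difference.

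The documents do not establish that the error differs by arm, in which direction, or by how much. Under the assumed error rates, a 5- or 10-point instrument difference against a 20-point design effect is enough to take power well below the planned 80%. A 10-point difference with no true effect produces a false result roughly ten times as often as the nominal 2.5%. These figures show sensitivity and do not predict what will happen.

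**What to change.** 1. Reconcile section {18b}, section {11c} and the Phase 3 description, including whether controls use the app and for what.
2. Name the weekly spreadsheet, already requested from both arms, as the primary adherence source. Specify that it captures minutes and self-rated intensity identically in both arms, since section {11c} speaks only of activity carried out and a 70% rule needs more than that.
3. Score it with one 70% rule, applied by someone blind to arm.
4. Report IG app and biosensor adherence as supportive. Add a sensitivity analysis over a range of self-report error, informed by IG's paired spreadsheet and device records, noting that error estimated in IG need not carry over to CG.
5. State as a limitation that the self-report is unblinded and that IG receives device feedback, so reporting error may still differ by arm.

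**Cost.** Changes to protocol and analysis plan wording, and a defined spreadsheet layout; if the present spreadsheet does not hold minutes and intensity, those fields must be added. The main downside is that the primary measure in IG becomes less objective than the app and biosensor record.

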### Data management {19}

Characterization data collection and evaluation result recording will be documented on paper forms. Subsequently, the principal investigator or their delegate will input the data into an Excel spreadsheet. Another investigator will review this data entry to mitigate potential errors.

### Confidentiality {27}

All participant information will be securely stored in locked file cabinets, located in restricted-access areas, for a duration of 5 years post-study completion.

### Plans for collection, laboratory evaluation, and storage of biological specimens for genetic or molecular analysis in this trial/future use {33}

See the “ Additional consent provisions for collection and use of participant data and biological specimens {26b}” section; there will be no biological specimens collected.

## Statistical methods

### Statistical methods for primary and secondary outcomes {20a}

Data distribution will be assessed using the Kolmogorov–Smirnov test. Parametric data will be presented as mean ± standard deviation, while non-parametric data will be displayed as median (interquartile range). In phase 1, resting and maximum HR assessed by both the Polar H10 monitor and the test biosensor will be compared using either *t*-test or Wilcoxon test, based on data distribution. The same comparison will be applied to the step count measured by the test biosensor and the ActiGraph triaxial accelerometer. Intraclass correlation coefficient (ICC) will also be computed, along with Bland–Altman analysis to assess HR and step count agreement.

During phase 2, a quantitative analysis will be conducted on the frequency of possible gamified application failures. Pre- and post-exercise protocol data, including functional capacity, VO_2_, tissue oxygenation, maximum and resting HR, systemic blood pressure, and perceived exertion, will be compared using *t*-test or Wilcoxon test, based on data distribution. Similarly, the number of steps evaluated by the biosensor under test and the ActiGraph accelerometer will undergo the same analysis, along with ICC calculation.

For phase 3, a qualitative analysis will be performed on participants’ diary reports and a quantitative assessment of potential gamified application failures. Step count measured by the biosensor will be compared to the ActiGraph accelerometer using Student’s *t*-test or Wilcoxon rank-sum test, depending on residual distribution. Agreement between step counts will be evaluated using Bland–Altman test, Lin’s correlation coefficient, and intraclass correlation coefficient. Pre- and post-exercise protocol data, encompassing functional capacity, VO_2_, tissue oxygenation, maximum and resting HR, systemic blood pressure, subjective exertion perception, endothelial function, and HRV, will be analysed using Student’s *t*-test for paired samples or Wilcoxon signed-rank test, aligned with residual distribution. Participants achieving a minimum of 70% completion of the prescribed protocol will be classified as adherent. As the random allocation is anticipated to ensure baseline comparability between the control and intervention groups, unadjusted analyses will primarily be carried out. In the event of any non-comparability in baseline characteristics due to chance, appropriate adjustments will be made to prevent potential biases. Significance level will be set at *p* < 0.05. The data will be analysed using Statistical Package for the Social Sciences (SPSS) 20.0 (SPSS, Chicago, IL, USA).

For the progression of our study through its phases, we have set clear criteria to determine the acceptability of outcomes: *Phase 1*: We regard the study as satisfactory if the standard error between the biosensor under test and the reference measurements is within 5%. If this criterion is not met, we would reconsider moving to the next phase until the discrepancies are addressed. *Phase 2*: The study’s progression will depend on the functionality of the application. Should there be serious errors within the application that prevent exercise or significantly hinder adherence, we would need to address these issues before considering progression to phase 3. *Phase 3*: Here, our benchmark for continuation is achieving at least 70% adherence. Any value below this would prompt us to assess the reasons for the reduced adherence and potentially re-evaluate our approach. Additionally, it is important to note that throughout all phases, we have ensured that there are no operational issues related to the app. Thus, significant data recording failures in earlier phases would indeed influence our decision to proceed to the next phase.

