## Intervention description {11a}

### Phase 1: Functional assessment and biosensor validation

Following the development of the wearable biosensor designed for heart rate and step count monitoring, a validation test will be conducted during the incremental shuttle walk test (ISWT) [18, 19]. This ISWT is a recognized, reliable, and secure walking test for assessing functional capacity. Throughout the evaluation, participants will wear the biosensor on their nondominant wrist to capture HR and step data. For HR measurement, the Polar H10 chest strap (Polar Electro Oy, Kempele, Finland) will serve as the reference [20], while the triaxial Actigraph GT3X accelerometer (Actigraph, Pensacola, Florida) will be used on the nondominant wrist to measure step count [21].

The assessment will encompass several variables, including maximum distance, top speed, oxygen consumption (VO_2_), tissue oxygenation, and blood pressure (measured at the test’s outset and conclusion). Continuous HR tracking will be achieved by both the biosensor under evaluation and the Polar H10 monitor. Additionally, perceived exertion will be recorded using the modified Borg scale [22]; other data to be captured include the stage and corresponding stage at which the test is stopped. Two ISWTs will be conducted, with a maximum interval of one week between them. The results from the most successful trial will be utilized for subsequent analyses. This phase will be executed within a research laboratory environment by trained researchers.

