#### Prescription of physical exercise

Building upon the ISWT results, the intensity of physical exercise will be tailored. The training protocol will span six weeks, with sessions conducted 5 days a week. The training volume will encompass a minimum of 300 min weekly at moderate intensity (40–60% of heart rate reserve) or a minimum of 150 min weekly at vigorous intensity (60–80% of heart rate reserve) [26]. The training will involve a one-step staircase (20 cm height, 60 cm length, and 40 cm width). The target intensity will range from 40 to 80% of the heart rate reserve, calculated based on ISWT. The heart rate reserve will be determined by subtracting the resting heart rate from the maximum heart rate achieved during the functional test. Throughout the exercise session, both HR monitors (Polar H10) and the test biosensor will be closely monitored.

The gamified smartphone application will offer visual feedback on intensity and heart rate, alongside researcher observation of heart rate measured by Polar H10 and the biosensor linked to the gamified application. Additionally, the biosensor, equipped with an accelerometer, will track step count during training. Phases within the scenario will be defined using gamification techniques, incorporating rewards, competitions, and other strategies to ensure adherence and engagement across varying intensities, including warm-up, maintenance, and cool-down phases.

In the initial week, sessions will last 30 min: a 5-min stationary gait warm-up, 20 min of step interval training (2 min at target HR and 3 min at low intensity), and a 5-min stationary gait cool-down. Over the subsequent 5 weeks, each session will extend to 60 min: a 5-min stationary gait warm-up, 50 min of step training at target HR, and a 5-min stationary gait cool-down. Sessions will occur at least twice a week and no more than five times. To meet the minimum adherence criterion, participants must achieve at least 70% of the prescribed training volume outlined in the protocol. Upon completing the 6-week training program, a new functional capacity assessment will be conducted.

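### Phase 1 names only resting and maximum HR for the device comparison, so the named test cannot see sensor error at 40–80% of heart rate reserve, where the sensor is used

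*Protocol article*

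**What the plan says.** The Outcomes section {12} lists as the first primary outcome "the concordance between HR and step count measurements assessed by the biosensor under test compared to standard devices". Under Phase 1 the biosensor is worn on the wrist, and "Continuous HR tracking will be achieved by both the biosensor under evaluation and the Polar H10 monitor". A continuous paired HR record will therefore exist for each participant.

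The phase 1 paragraph of the statistical methods section {20a} then says that "resting and maximum HR assessed by both the Polar H10 monitor and the test biosensor will be compared using either" a t-test or a Wilcoxon test, depending on distribution. Steps get the same comparison. An ICC "will also be computed, along with Bland–Altman analysis to assess HR and step count agreement". No HR values other than rest and maximum are named in that paragraph.

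The sensor's later use is set out under Prescription of physical exercise: "The target intensity will range from 40 to 80% of the heart rate reserve, calculated based on ISWT". That section defines the reserve as the maximum HR reached in the functional test minus resting HR.

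For phases 2 and 3, the device comparisons in {20a} concern step counts only. HR appears there among the variables compared before and after training, not between devices.

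**The concern.** Two consequences follow from choosing rest and maximum.

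First, these are the two ends of the heart rate reserve scale. The device is built to hold a user between 40% and 80% of that scale, and neither value says anything directly about its error there. A paired test on the ends can be clean while the sensor misreads the training range. Phase 1 is also the only phase for which an HR agreement analysis is stated, and phase 3 uses the sensor outside the laboratory.

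Second, the text does not say that the two devices' maxima are read at the same moment. The largest of many noisy readings tends to lie above the true peak, and by more when the noise is larger. If each device contributes its own maximum, a wrist sensor with zero average error but more noise than the chest strap can look as if it reads high. The test would then report a systematic difference that a moment-by-moment comparison would not show.

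**Working it through.** **Inputs from the protocol.** Values compared: resting and maximum HR per device ({20a}). Reserve = ISWT maximum minus rest; target range 40–80% of it (Prescription of physical exercise). n = 15 for phases 1 and 2 (Sample size {14}); the stated recruitment figure is reproduced by 15 × 1.30 = 19.5, rounded up to 20, and is not in dispute here. Significance level 0.05 ({20a}), taken as two-sided.

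**Step 1: where the two values lie.** Percent of reserve = (HR − rest) / (maximum − rest). At rest this is 0%; at the ISWT maximum it is 100%. Both lie outside 40–80%.

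**Step 2: what an error inside the range does.** Assume rest 70 and maximum 170 bpm, so the reserve is 100 bpm. Then 40% is 110, 60% is 130 and 80% is 150 bpm. Let the sensor be exact at both ends and wrong by *b* bpm at 130:

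| *b* (bpm) | *b*/130 | shift in reserve, *b*/100 | difference at rest | difference at maximum |
|---|---|---|---|---|
| 5 | 3.8% | 5 points | 0 | 0 |
| 10 | 7.7% | 10 points | 0 | 0 |
| 15 | 11.5% | 15 points | 0 | 0 |
| 20 | 15.4% | 20 points | 0 | 0 |

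The case is constructed, but the last two columns do not depend on any noise assumption.

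**Step 3: each device's own maximum.** Write the sensor reading as S(t) = θ(t) + e(t) and the reference as R(t) = θ(t) + u(t), with both errors averaging zero. The time-matched difference S(t) − R(t) averages zero. The difference max S − max R averages above zero when e is more variable than u.

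To size this, 600 studies of n = 15 were simulated per setting. All of the following are assumptions, because the article gives no sampling rate, averaging window or noise level: true HR rising linearly from 75 to 175 bpm over 12 min, one reading every 5 s, reference SD 1 bpm, sensor noise independent or with autocorrelation 0.8, and either no smoothing or a 30-s average.

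| Sensor SD (bpm) | Unsmoothed: mean difference; rejection | 30-s average: mean difference; rejection |
|---|---|---|
| 1 (as reference) | about 0; 4–5% | about 0; 3–5% |
| 3 | +1.0 to +2.2; 27–98% | about +0.1; 5–6% |
| 5 | +2.9 to +5.0; 71–100% | +0.5 to +0.8; 12–13% |
| 10 | +9.2 to +13.3; 99–100% | +2.1 to +3.9; 54–60% |

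As a check on one cell, take SD 5, autocorrelation 0.8, unsmoothed: mean 2.91, SD of differences 4.18. Then 2.91 / (4.18/√15) = 2.91 / 1.08 = 2.7 standard errors, in line with 71% rejection. With 30-s averaging: 0.81 / (3.90/√15) = 0.81 / 1.01 = 0.8 standard errors, in line with 12%.

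**Step 4: after the change.** Reading both devices at the same moment at the end of the test gave mean differences between −0.08 and +0.10 bpm and rejection of 3–6% in every setting.

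**The case against.** **Agreement statistics are planned.** ICC and Bland–Altman fit the concordance outcome better than the t-test, and their sentence does not limit HR to rest and maximum. A reader might infer that mid-range error will escape every planned analysis. The text does not support that: the continuous record is not excluded, so the blind spot is certain only for the t-test or Wilcoxon. What remains is that no other HR readings are named for the agreement statistics, so the natural reading carries the same two values over.

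**An article leaves detail to a fuller document.** That covers sampling rate and the form of the Bland–Altman. It does not cover the choice of quantity, which the article does state.

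**The upward difference at maximum is conditional.** It needs each device's own maximum, no time-matching, and a sensor noisier than the reference after any smoothing. A reader might infer that phase 1 will show this bias; the documents do not establish any of those conditions.

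**Rest and maximum are not arbitrary.** They define the reserve, so they matter for the prescription. This stands, and is a reason to keep them as additional comparisons.

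**Phase 2 watches both HR devices in supervised sessions.** True, and it gives practical reassurance before unsupervised use. No HR agreement analysis of those data is stated.

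**The go/no-go rule is not the t-test.** Progression from phase 1 depends on a standard error within 5%, with the HR points unnamed. A reader might infer that a false bias at maximum would block progress. Read as percent error, +5.0 bpm at 175 bpm is 2.9%, inside the limit; only the noisiest unsmoothed setting (+13.3/175 = 7.6%) would exceed it. No effect on the decision can be claimed.

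**One of two ISWTs.** The plan states "Two ISWTs will be conducted, with a maximum interval of one week between them" and "The results from the most successful trial will be utilized for subsequent analyses". A reader might take this as a source of the bias. It is not. Using both tests would multiply the standard error of the mean difference by √((1 + r)/2), which is 0.77 at an assumed between-test correlation of 0.2 and 0.95 at 0.8. That is an efficiency point only.

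**Conclusion.** The point holds in limited form. For a primary outcome of HR concordance, with continuous paired data collected, the only HR quantities named for phase 1 lie at 0% and 100% of reserve. The named test has no ability to detect error confined to 40–80%; this follows from the protocol's own definitions. Whether ICC and Bland–Altman share the gap is open, because their HR input is not stated, and phases 2 and 3 state no HR agreement analysis that would close it.

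The false positive difference at maximum is a possibility, not a prediction. Under the assumed noise it runs from about 0 (low noise, or 30-s averaging at modest noise) to about +5 bpm at SD 5 unsmoothed, and up to +13.3 bpm at SD 10 unsmoothed. The change is worth making because it concerns a primary outcome and uses recordings already planned.

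**What to change.** In the phase 1 paragraph of {20a}, state that HR agreement (Bland–Altman and ICC) is assessed on biosensor and Polar H10 readings paired at the same time points across the ISWT, for example at the end of each stage. Calculate limits of agreement by a method that allows for repeated measurements within a participant. Report the mean difference and limits separately for readings within 40–80% of heart rate reserve.

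Keep resting and maximum HR as additional comparisons, and define maximum as the value on both devices at one common time or over one common window.

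The cost is aligning two recordings that are already made, and a repeated-measures Bland–Altman in place of the simple one. No new participant or measurement is needed.

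### Step-count agreement is not normalised for a walk that each person stops at a different stage, so a high ICC need not mean an accurate sensor

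*Protocol article*

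**What the plan says.** All places are in the Protocol article.

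- **Outcomes {12}:** the first primary outcome is "the concordance between HR and step count measurements assessed by the biosensor under test compared to standard devices", the standard devices being the Polar H10 for heart rate and the ActiGraph for steps.
- **Phase 1: Functional assessment and biosensor validation:** the biosensor is validated during the ISWT. The stopping point is recorded for each person: "other data to be captured include the stage and corresponding stage at which the test is stopped". Two tests are done, and "The results from the most successful trial will be utilized for subsequent analyses", so one test per person is analysed.
- **Statistical methods {20a}, phase 1:** after comparing resting and maximum heart rate between devices, the section adds: "The same comparison will be applied to the step count measured by the test biosensor and the ActiGraph triaxial accelerometer". Agreement follows: "Intraclass correlation coefficient (ICC) will also be computed, along with Bland–Altman analysis to assess HR and step count agreement".
- **Same section, phase 2:** step counts get a paired comparison and an ICC.
- **Same section, phase 3:** "Agreement between step counts will be evaluated using Bland–Altman test, Lin’s correlation coefficient, and intraclass correlation coefficient". Lin's coefficient appears only here, and the section does not say whether these steps come from the ISWT or from home sessions.
- **Same section, progression criteria:** phase 1 is satisfactory if "the standard error between the biosensor under test and the reference measurements is within 5" per cent.

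The article nowhere says whether the step count is a test total, a count per stage or a rate. It mentions no adjustment for duration and no percentage, log or ratio limits.

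**The concern.** The ICC and Lin's coefficient both set device error against the spread between people. In an incremental test that people leave at different stages, total steps vary between people mainly because walking time varies. That spread says nothing about the sensor, yet it pulls both coefficients towards 1. A sensor with a sizeable percentage error could therefore be reported with a high coefficient on a primary outcome.

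The second issue is scale. If device differences grow with the number of steps, limits of agreement expressed as one fixed number of steps are too wide for people who stop early and too narrow for those who walk longest. The plan's own phase 1 criterion is a percentage, and limits in raw steps cannot be set beside it: 5% of a short walk is fewer steps than 5% of a long one.

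**Working it through.** The article gives no ICC, limits of agreement, step-count SD or walking time, so there is no stated figure to reproduce. The inputs below are assumptions.

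**Inputs (assumed):** total steps = walking time × cadence, mean 920; walking-time SD d = 20, 30 or 40% of its mean; cadence SD c = 8%; ActiGraph count taken as true; biosensor = true count × (1 + b + error), with error SD e = 10% or 5% and b = 0 or −10%.

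**Formula.** With V the squared coefficient of variation of the analysed count, V ≈ d² + c² for totals and V = c² for steps per minute. In large samples the absolute-agreement ICC and Lin's coefficient are both

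2(1+b)V / [V + (1+b)²V + e²(1+V) + b²],

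which for b = 0 is V / [V + ½e²(1+V)].

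**No bias, 10% error:**
- d = 20%: V = 0.04 + 0.0064 = 0.0464; 0.0464 / (0.0464 + 0.0052) = 0.90
- d = 30%: V = 0.0964; 0.0964 / (0.0964 + 0.0055) = 0.95
- d = 40%: V = 0.1664; 0.1664 / (0.1664 + 0.0058) = 0.97 (0.966 before rounding)
- steps per minute: V = 0.0064; 0.0064 / (0.0064 + 0.0050) = 0.56

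Walking time supplies 0.04/0.0464 = 86% of the spread in totals at d = 20% and 0.16/0.1664 = 96% at d = 40%.

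**No bias, 5% error:**
- d = 20%: 0.0464 / (0.0464 + 0.0013) = 0.97
- d = 40%: 0.1664 / (0.1664 + 0.0015) = 0.99
- steps per minute: 0.0064 / (0.0064 + 0.0013) = 0.84 (0.836 with unrounded terms)

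**10% undercount plus 10% error:**
- d = 20%: 0.0835 / (0.0464 + 0.0376 + 0.0105 + 0.01) = 0.80
- d = 40%: 0.2995 / (0.1664 + 0.1348 + 0.0117 + 0.01) = 0.93
- steps per minute: 0.0115 / (0.0064 + 0.0052 + 0.0101 + 0.01) = 0.36

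A separate simulation with other assumed inputs (mean stopping time 9 minutes, 10% error) shows the same pattern. The coefficient on totals is 0.36 if everyone walks equally long, and 0.82, 0.94 and 0.97 for stopping-time SDs of 1, 2 and 3 minutes, with the sensor unchanged. The rise on totals appears whether the error is a fixed percentage per person, independent from minute to minute, or unrelated to the count.

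**Bland–Altman limits in raw steps.** With a 10% proportional error the half-width is 1.96 × 92 × √(1+V): 184 steps at d = 20% and 195 at d = 40%. A half-width of 184 steps is 184/920 = 20% at the mean count, 184/500 = 37% for a 500-step walk and 184/1,300 = 14% for a 1,300-step walk, although the true limits are about ±20% for everyone. Simulated coverage of nominal 95% limits depends on how the error behaves:

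| Error behaviour | Shortest third | Longest third |
|---|---|---|
| Proportional to the count | 98.8–99.8% | 86–90% |
| Grows with the square root of the count | 97–99% | 90–92% |
| Unrelated to the count | 95% | 95% |

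The Bland–Altman point is therefore conditional; the effect of walking time on the coefficients is not.

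**The case against.** **Totals are an inference.** The article says only step count. The unit and the Bland–Altman scale are details that a condensed article may leave to a fuller document. This stands as a limit on the claim. But the same paragraph does specify the heart-rate variables (resting and maximum), one test per person is analysed, and a bare step count for one test reads most naturally as its total.

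**Wrong limits.** A reader might infer that the Bland–Altman limits must be wrong at both ends. The documents do not support that. They do not prescribe constant limits, and they do not show that differences grow with the count. If differences do not grow, constant limits are correct.

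**Phase 3.** A reader might also apply the argument to Lin's coefficient in the ISWT. Lin's coefficient is planned only for phase 3, where the source of the steps is not given. If the steps come from home sessions, the stopping-stage argument does not carry over as it stands.

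**Consequence.** No ICC or Lin threshold decides anything; phase 1 progression rests on the 5% rule. A paired comparison and Bland–Altman analysis are reported beside the phase 1 ICC, and a 10% undercount would show as a mean difference of about −92 steps in 920. This stands: the coefficient can mislead when read alone, but it does not control the trial.

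**Preference.** Every ICC depends on the spread of its sample. The 0.56 per minute rests on an assumed narrow cadence spread and is no truer than 0.90, and counting steps is what the biosensor is for. This stands too, and is why the rate-based coefficient should sit beside the totals rather than replace them.

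**Conclusion.** The point holds in conditional form. If the phase 1 step count is the ISWT total, the ICC largely measures differences in walking time and can look high for a sensor with sizeable percentage error. The same applies to the phase 3 ICC and Lin's coefficient if they use ISWT totals.

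Under the stated assumptions the gap is 0.90–0.97 on totals against 0.56 per minute at 10% error, and 0.97–0.99 against 0.84 at 5% error, so it narrows as the sensor improves. Walking-time spread, cadence spread and error size are all assumed. With the 15 participants planned for phases 1 and 2, any coefficient would also be imprecise. Constant raw-step limits are a problem only if differences grow with the count, which the data can show. The practical risk is that a coefficient driven by duration is read as sensor accuracy on part of a primary outcome.

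**What to change.** In Statistical methods {20a}, for phase 1, and for phase 3 if ISWT steps are used:

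1. State the unit of the step count and, for phase 3, whether the steps come from the ISWT or from home sessions.
2. Run Bland–Altman for steps on the percentage difference or log ratio (biosensor/ActiGraph), alongside the raw limits, and check whether differences grow with the count. Step agreement is then on a percentage scale like the 5% criterion. It does not stand in for that criterion, because the standard error named there is not defined.
3. Report the ICC (and Lin's coefficient in phase 3) on steps per minute, or per ISWT stage with participant as the cluster, beside the value on totals.
4. Say that the coefficient on totals will not be read alone as sensor accuracy.

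The cost is a little more analysis and a lower coefficient printed next to the totals value. Both devices' counts, the distance and the stopping stage are already collected, and heart rate is tracked continuously, so walking time should be recoverable. The per-stage version also needs time-stamped step counts, which the article does not mention; steps per minute does not.
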